At the time of writing, the most frequently provided CAMs in private and public oncology centers in European countries are mind-body techniques, acupuncture, homeopathy, energy therapies, health promotion, traditional herbal medicine, as well as manipulation and body-based practices (kinesiology, osteopathy, physiotherapy, and reflexology) [4]. Foot reflexology is a holistic approach. A systematic review indicated that foot reflexology seems to be effective for patients with cancer but this field requires further rigorous research with a randomized controlled trial [5]. More specifically, foot reflexology improved the quality of life of patients in the palliative stage of cancer [6], significantly decreased pain intensity and anxiety in patients with metastatic cancer [7], and significantly decreased the perceived pain and anxiety of postoperative patients with gastric cancer and hepatocellular cancer [8]. Moreover, a significant decrease in chemotherapy-induced nausea and vomiting (CINV) was observed in patients with breast cancer who received reflexology treatments [9,10]. Foot reflexology, used concomitantly with conventional treatment, shows promise in decreasing the side effects induced by chemotherapy. In particular, it may decrease CINV, which is the side effect that concerns patients the most [11], as it decreases their overall quality of life [12,13] and induces metabolic complications [11]. In addition, CINV can lead to dose reduction, postponement of treatment, and even discontinuation of treatment [14], all of which can decrease the effectiveness of the treatment [15]. To control acute and delayed CINV, antiemetic drugs are prescribed; the main ones used are 5-hydroxytryptamine 3 receptor antagonists, dexamethasone, and neurokinin-1 inhibitor receptor antagonists [11,16,17]. But despite antiemetic therapy, CINV may persist [13]. In addition to the emetogenicity of the chemotherapy, various parameters may be associated, including risk factors (age, gender, alcohol use, history of motion sickness, and history of pregnancy-related vomiting) [12], treatment compliance [18] and the perceptual gap between health professionals and patients [19,20].

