In 2018, in both sexes combined, lung cancer was the leading global cause of cancer death (18.4%), followed by digestive system cancer including colorectal (9.2%), stomach (8.2%), and liver (8.2%) [21]. According to national and international recommendations, adjuvant treatment for lung and digestive system cancer is platinum-based chemotherapy [22-26]. Anticancer therapy cisplatin has a high emetic risk (incidence of CINV >90%), while carboplatin and oxaliplatin have a moderate emetic risk (incidence of CINV is from 30% to 90%) [17].

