## Methods

### Trial Design

An open-label randomized controlled trial (RCT) will be carried out, in which patients are randomized to one of two groups at a 1:1 ratio: (1) conventional care with foot reflexology (40 patients) and (2) conventional care without foot reflexology (40 patients). Randomization is stratified on the type of cancer (digestive system or lung) and the presence or absence of metastases. The sponsor is the Hospices Civils de Lyon. The principal investigator is [name]. To design this trial, we used the CONSORT Statement for Randomized Trials of Nonpharmacologic Treatments [27].

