### Eligibility Criteria of Participants

Eligibility requirements for this study are the following: patients aged ≥18 years; patients with lung cancer (eg, non–small cell lung carcinomas, small cell lung cancer, mesothelioma) or digestive system cancer (eg, colorectal cancer, pancreatic cancer, liver cancer); patients on platinum-based chemotherapy with or without radiation therapy concomitant (eg, digestive system cancer: FOLFOX, FOLFIRINOX, GEMOX, LV5FU2-CDDP; lung cancer: cisplatin-vinorelbine, pemetrexed-cisplatin, pemetrexed-carboplatin, carboplatin-paclitaxel); World Health Organization performance status ≤2; patients affiliated to the national social security system or equivalent; patients able to complete the questionnaires (comprehension of oral and written French language); and patients who provide written informed consent. The exclusion criteria are phlebitis; vena cava syndrome; weight loss >5% in the 3 months before inclusion date; uncontrolled pain; patients receiving morphine or morphine derivatives; brain metastases; patients receiving foot reflexology outside the study; patients under guardianship or curatorship or who have been deprived of their rights. All data will be collected from outpatients and inpatients.

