### Type of Statistical Analysis Used

Study data are entered into a password-protected Excel spreadsheet (version 14.0, Microsoft Corp) accessible only to the project manager. Quantitative data will be described for the entire population, using the following descriptive statistics: the number, the number of missing values, the mean, the standard deviation, the median, the interquartile range, and the range. Qualitative variables will be summarized for the entire population using the following descriptive statistics: the frequency and percentage for each category of the variable and the missing values (missing values will be counted but are not included in the denominator of the calculation of frequencies).

For the primary endpoint, comparison of the relative change in the VAS between the two groups will be performed using a linear model adjusted on the type of cancer (digestive system or lung) and the presence of metastases (randomization stratification factors). This model allows the estimation of the difference in mean relative variation of VAS between the two groups, adjusted on potential confounding factors, with a 95% confidence interval. The VAS score may be transformed satisfy the assumptions of the linear model. If the assumptions of the model cannot be verified, the comparison between the two groups will be done using the van Elteren test. Specific estimates of the difference in relative VAS variation between the groups will be provided for both types of cancer, and by metastatic status.

The comparison of the frequency of episodes of CINV between chemotherapy cycles between the two groups will be performed using a mixed effects Poisson model, integrating the number of intercycle days as offset. The model will consider the intervention group and stratification criteria as fixed effects, and will incorporate one random intercept per patient.

The proportion of chemotherapy cycles in which the patient took at least one antiemetic drug will be compared between the two groups using a mixed effect logistic regression model. The model will consider the intervention arm and stratification criteria as fixed effects, and will incorporate one random intercept per patient.

The comparison of quality of life and anxiety between the two groups will be done using a Wilcoxon test.

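### The CINV frequency model takes calendar intercycle days as exposure although episodes come only from a patient diary, and it leaves out the platinum agent

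*Protocol article*

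**What the plan says.** Under Type of Statistical Analysis Used, the protocol article compares the frequency of CINV episodes between chemotherapy cycles "using a mixed effects Poisson model, integrating the number of intercycle days as offset". The covariates are fixed in the next sentence: "The model will consider the intervention group and stratification criteria as fixed effects, and will incorporate one random intercept per patient". The stratification criteria are given under Trial Design: "Randomization is stratified on the type of cancer (digestive system or lung) and the presence or absence of metastases". The platinum agent is therefore neither a stratification factor nor a term in the model.

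The counts come from a diary that patients are to fill in daily from the first to the fourth cycle (Secondary Outcomes, Nausea and Vomiting). The section Description of Processes, Interventions, and Comparisons uses the same diary to measure adherence to reflexology and the perceived effect of self-massage. It also gives a cycle length of 2 or 3 weeks, depending on the regimen.

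The Background states that "CINV can lead to dose reduction, postponement of treatment, and even discontinuation of treatment". On the agents it states: "Anticancer therapy cisplatin has a high emetic risk (incidence of CINV >90%), while carboplatin and oxaliplatin have a moderate emetic risk", the moderate class having an incidence of 30% to 90%. The Eligibility Criteria allow agents of both classes in lung cancer, "lung cancer: cisplatin-vinorelbine, pemetrexed-cisplatin, pemetrexed-carboplatin, carboplatin-paclitaxel", and list a cisplatin regimen (LV5FU2-CDDP) beside oxaliplatin regimens such as FOLFOX in digestive system cancer.

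**The concern.** An offset should measure the time over which events could have been recorded. Here the numerator is what patients wrote down and the denominator is the calendar. The two agree only if every diary day is filled in. A blank day lowers the recorded rate, and the arm with more blanks looks better. The trial is open label, and intervention patients have an extra reason to keep the diary because it also serves their reflexology follow-up. A completion difference between arms is therefore plausible, though the article does not show one.

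The denominator can also depend on the outcome. If CINV delays the next cycle, as the Background says it can, patients with worse CINV may gain exposure days. Where those days carry few episodes, their rate is diluted. If reflexology works, control patients would be the more delayed, and a real benefit would be understated.

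Separately, the article's own emetic classes mark the platinum agent as strongly prognostic, and cancer type captures it only in part. Leaving it out gives away precision and leaves a chance imbalance between arms unadjusted.

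At stake is the only between-group test of intercycle episode counts that the article describes. The abstract's objective names frequency beside severity, although the Evaluation Criteria list the diary outcome as secondary.

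**Working it through.** **The plan's own figures.** The article gives no episode rate, power, postponement rate or diary completion for this outcome. Its only sample-size figure is 40 per group for the VAS endpoint: 2 × [32.2 × (1.960 + 1.282) / 24]² = 37.8, so 38 per group by the normal approximation and 39 by the t test. That is close to the stated 40, and nothing below bears on it. All completion, delay and agent inputs below are assumptions.

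**1. Blank diary days.** Let c be the proportion of days completed, and assume that blank days would have had the same episode rate as completed ones. With calendar days as offset, the estimated ratio (intervention/control) is the true ratio × c(intervention) / c(control).

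| Control | Intervention | Factor |
|---|---|---|
| 70% | 70% | 1.00 |
| 75% | 90% | 0.90/0.75 = 1.20 |
| 90% | 75% | 0.75/0.90 = 0.83 |
| 70% | 90% | 0.90/0.70 = 1.29 |
| 90% | 70% | 0.70/0.90 = 0.78 |

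**2. Postponement.** Assume a 7-day delay in a proportion p of cycles, and that the extra days add no episodes. The ratio is then multiplied by mean control days / mean intervention days, where mean days = base + 7p.

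- Delays of 20% in both arms: 1.00.
- 30% control, 10% intervention, 14-day cycles: (14 + 2.1)/(14 + 0.7) = 16.1/14.7 = 1.095.
- The same with 21-day cycles: (21 + 2.1)/(21 + 0.7) = 23.1/21.7 = 1.065.
- 10% control, 30% intervention: 14.7/16.1 = 0.913 and 21.7/23.1 = 0.939.

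With a true ratio of 0.70 and control patients delayed more, 0.70 becomes about 0.70 × 1.065 = 0.75 to 0.70 × 1.095 = 0.77. That is a shift towards no effect.

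**3. Simulation of the model.** There were 800 trials per scenario, each with 80 patients (half lung, half digestive), three intercycle periods and a log-link Poisson model with a gamma patient effect. Cisplatin was assumed to double the rate and to be given to 50% of lung and 10% of digestive patients.

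- Completion 70% control v 90% intervention, true ratio 1.00: calendar offset 1.302, completed-days offset 1.013.
- Completion 90% v 70%, true ratio 1.00: calendar offset 0.780, completed-days offset 1.003.
- Delays 30% v 10%, diary complete, true ratio 1.00: calendar offset 1.089, completed-days offset also 1.089, equal exposure per cycle 1.011. Completed diary days therefore repair the blank-day problem but not the postponement one.
- Agent omitted v included, no delays or blanks: mean ratio 1.004 v 1.005 (true 1.00) and 0.696 v 0.694 (true 0.70). The SD of the log ratio falls from about 0.19 to 0.17-0.18.

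**4. Chance imbalance in the agent.** If one third receive cisplatin, the SD of the difference in share between arms of 40 is √[(1/3)(2/3)(2/40)] = 0.105. A difference of at least 10 points has probability 0.34 by the normal approximation. The exact figure for at least 4 patients is 0.41, or 0.34 when arms are balanced by cancer type with the shares in step 3. Under the assumed doubling, a 10-point imbalance around one third shifts the ratio by (1 + 0.383)/(1 + 0.283) = 1.08, which is 0.075 on the log scale against an SD of about 0.19.

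**The case against.** An offset for time between cycles is the conventional choice when cycles last 2 or 3 weeks, and the stated target is the frequency between cycles. The diary is meant to be filled in daily, so by design diary days equal intercycle days. Handling of missing entries is commonly left to the analysis plan, which is not shown. Adjusting for the stratification factors is standard, and the random intercept takes up unexplained differences between patients.

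Much of this stands. Silence on missing entries is no finding, and the planned difference between 2- and 3-week regimens is what an offset is for. But the article does fix the exposure as intercycle days, and that rule counts a blank day as observed. The criticism is of the stated rule.

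Some stronger readings are tempting and not supported:

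- *Postponed cycles and blank days as such change the ratio.* They do not when they are equal between arms; steps 1 and 2 then give 1.00.
- *A one-week postponement produces a 33% reduction.* Ten episodes give 10/14 = 0.714 per day or 10/21 = 0.476 per day, but this compares two single cycles. As an arm contrast it would need every cycle in one arm to be delayed and none in the other.
- *Episodes are known to cluster after infusion.* The article mentions acute and delayed CINV but gives no time course, so few episodes on extra days remains an assumption.
- *The agent is the main prognostic factor and omitting it biases the comparison.* The Background also lists age, gender, alcohol use, motion sickness and pregnancy-related vomiting, and ranks none of them. Under randomisation and a log link, step 3 shows no bias.
- *A fixed post-infusion window should replace the intercycle analysis.* It answers a different question and drops later episodes.

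**Conclusion.** The point holds as a conditional weakness of a secondary analysis. With calendar days as offset, the rate ratio is distorted by the ratio of diary completeness between arms: 1.20 at 90% against 75%, and 0.78 or 1.29 for a 20-point gap between 70% and 90%. There is no distortion if completion is equal. These figures assume that blank days resemble completed days; if patients leave blanks mainly on symptom-free days, the distortion is smaller.

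A 20-point arm difference in 7-day delays shifts the ratio by about 6-10% if the extra days add no episodes. If reflexology works and control patients are delayed more, the shift is towards no effect.

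Omitting the platinum agent causes no systematic bias. It costs some precision (SD of the log ratio about 0.19 against 0.17-0.18 under an assumed doubling of the rate) and leaves chance imbalance unadjusted. The documents supply none of the completion, delay or agent rates, so these sizes show sensitivity and not expected error.

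**What to change.** In the frequency model, replace the offset with the log of the number of diary days completed in each intercycle period. Add the platinum agent as planned at randomisation (cisplatin v carboplatin/oxaliplatin) as a fixed effect.

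Report, as a sensitivity analysis and not as the replacement, the same model restricted to a fixed number of days after each infusion, equal for all regimens. This is the part that addresses postponement, which the completed-days offset does not. Tabulating completed diary days and intercycle length by arm would show whether either concern applies.

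The cost is one extra degree of freedom and minor programming. The diary already exists, and the regimen must be known at inclusion because eligibility depends on it; whether it is held in the analysis data should be confirmed. The change should be written down before episode counts are compared by arm.

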#### Secondary Outcomes

##### Nausea and Vomiting

The benefits of foot reflexology on CINV will also be assessed with the diary completed every day by patients between the first and fourth cycle of chemotherapy. Every day, the patient assesses the frequency of nausea and vomiting, recording each episode of nausea and emesis, and assessing the intensity of nausea and vomiting when it is at its highest with a Likert scale (response modalities: “Very low,” “Low,” “Low Moderate,” “Severe,” “Very severe,” “Unbearable”).

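### The two diary models pool successive intercycle periods without a period term, so a trend over cycles can leak into the group effect if the arms contribute unequal numbers of periods

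*Protocol article*

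**What the plan says.** All references are to the protocol article.

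- **Diary window.** Under Secondary Outcomes (Nausea and Vomiting) the diary is "completed every day by patients between the first and fourth cycle of chemotherapy". That implies three intercycle periods: after cycles 1, 2 and 3.
- **Episode frequency.** Type of Statistical Analysis Used plans a mixed Poisson model, "integrating the number of intercycle days as offset". Its terms are then listed: "The model will consider the intervention group and stratification criteria as fixed effects, and will incorporate one random intercept per patient".
- **Antiemetic use.** In the same section: "The proportion of chemotherapy cycles in which the patient took at least one antiemetic drug will be compared between the two groups", by mixed logistic regression. The terms match: "The model will consider the intervention arm and stratification criteria as fixed effects, and will incorporate one random intercept per patient".
- **Stratification criteria.** Trial Design defines them: "Randomization is stratified on the type of cancer (digestive system or lung) and the presence or absence of metastases". Cycle is not among them.
- **Stopping.** Background notes that "CINV can lead to dose reduction, postponement of treatment, and even discontinuation of treatment".

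The article gives no expected trend over cycles and no expected rate of discontinuation.

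**The concern.** Each patient can supply up to three successive records to each model, yet every covariate is fixed within the patient. Records from different cycles are therefore treated as exchangeable. A patient observed only after cycle 1 and a patient observed over all three periods are taken to inform the same constant rate, or the same constant probability of antiemetic use.

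This does no harm while both arms contribute the same mix of periods. Background gives a reason why they may not: nausea and vomiting can end chemotherapy early. If reflexology reduces symptoms, control patients could stop sooner and contribute mainly early periods. Any rise or fall over cycles would then enter the comparison between groups. At stake are the rate ratio for episodes and the odds ratio for antiemetic use.

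The covariate lists are written out in the article, so this is a stated specification that can be improved, not a detail left to an unseen analysis plan.

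**Working it through.** **The plan's own figure.** The article gives no figure for the diary models. Its only calculation is for the primary endpoint (difference 73.5 − 49.5 = 24 points, SD 32.2, two-sided 5%, 90% power): n = 2 × (1.960 + 1.2816)² × 32.2² / 24² = 37.8, so 38 per group (39 with the t distribution), against 40 stated. It reproduces and has no bearing on this point.

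**Why offset and random intercept do not help.** For patient i in period j, let the count have mean t_ij × exp(η_i), where η_i holds group, strata and random intercept. Multiplied over periods, the likelihood depends on the data only through the total count Y_i = Σ y_ij and the total days T_i = Σ t_ij. Which periods make up T_i is lost.

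**Closed-form size under no treatment effect.** Assumptions, none from the documents: equal period lengths; rate multiplied by r per cycle; a fraction d stopping after each period, independently of outcome. Relative to period 1, a patient's average log rate is

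- one period (probability d): 0
- two periods (probability (1−d)d): ln[(1+r)/2]
- three periods (probability (1−d)²): ln[(1+r+r²)/3]

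When patients differ widely, the model weights them about equally, so the spurious log rate ratio is roughly the difference in the mean of these values.

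For r = 0.7 the two logs are −0.1625 and −0.3147.

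- Control, d = 0.30: 0.21 × (−0.1625) + 0.49 × (−0.3147) = −0.188
- Reflexology, d = 0.10: 0.09 × (−0.1625) + 0.81 × (−0.3147) = −0.270
- Difference −0.081; rate ratio exp(−0.081) = 0.92

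At the other extreme, with no variation between patients, the pooled rates are 1.7301/2.19 = 0.790 and 2.0269/2.71 = 0.748; ratio 0.95.

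**Simulation under no treatment effect** (40 per arm, three 14-day periods, 0.3 episodes per day at the start, random-intercept SD 0.8, strata not simulated; 400 Poisson and 600 logistic data sets per row). Stopping is per interval, control / reflexology. The true ratio is 1.

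| Model | Trend per cycle | Stopping | Closed form | As written | With period term | Rejection at 5%: as written / with term |
|---|---|---|---|---|---|---|
| Poisson, RR | ×0.7 | 30% / 10% | 0.92 | 0.92 | 0.99 | 9.8% / 6.5% |
| Poisson, RR | ×0.7 | 40% / 5% | 0.87 | 0.87 | 0.99 | 12.8% / 7.5% |
| Poisson, RR | ×0.85 | 30% / 10% | 0.96 | 0.96 | 1.00 | 4.0% / 3.5% |
| Poisson, RR | ×1.4 | 30% / 10% | 1.10 | 1.09 | 1.00 | 7.5% / 6.0% |
| Poisson, RR | ×0.7 | 15% / 15% | 1.00 | 0.99 | 0.99 | 7.0% / 7.7% |
| Poisson, RR | none | 30% / 10% | 1.00 | 1.01 | 1.01 | 5.5% / 5.8% |
| Logistic, OR | OR 0.5 | 30% / 10% | – | 0.88 | 0.98 | 5.8% / 3.2% |
| Logistic, OR | OR 0.5 | 40% / 5% | – | 0.83 | 1.02 | 7.2% / 4.0% |

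The Monte Carlo error of the rejection rates is at most about 1.7 points. The two rows with equal stopping or no trend show that both conditions are needed.

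**A different stopping pattern** (stopping only after period 1, patient SD 1, six episodes in period 1). With a 40% fall per cycle and 35% v 10% stopping, the rate ratio is 0.91 as written and 1.01 with the term. Closed form: (0.90 − 0.65) × ln(1.96/3) = −0.106, ratio 0.90. A 40% rise gives 1.10 against 1.00. A milder case (25% fall, 25% v 10%) gives 0.98 against 1.01.

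**The route the article itself describes** (a real effect, true rate ratio 0.60, stopping driven by observed symptoms). As written, the estimate is 0.58 with a falling trend (×0.7) and 0.63 with a rising one (×1.4); with the period term it is 0.60. The distortion is 0.58/0.60 = 0.97 and 0.63/0.60 = 1.05, that is 3% to 5%.

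**The case against.** The strongest reply is that both conditions are hypothetical, and the article supplies neither a trend nor a stopping rate. That stands: every size above is conditional on assumptions.

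Next, the null simulations impose unequal stopping with no treatment effect, whereas the reason given for unequal stopping presupposes an effect. That is fair, and it is why the run with a true effect and symptom-driven stopping matters. The distortion persists there, but it is smaller.

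Third, the bias is small against the precision available. With patient SD 1 and 40 per arm, the standard error of the log rate ratio is about √(2 × 1.15/40) = 0.24, where 1.15 is an approximate variance that allows for Poisson noise. A shift of 0.106 is then about 0.4 standard errors. In the moderate case (×0.85, 30% / 10%) the rejection rate is not inflated at all. This also stands.

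Fourth, the article does not say how its rule for the analysis set, which requires a completed endpoint evaluation, applies to the diaries. Whether a patient with a single period enters these models is therefore an assumption.

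Fifth, the article is condensed, and a period term might appear in an analysis plan. This carries less weight, because the fixed effects are listed explicitly for both models and a plan that followed the list would omit the term.

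A reader might also fault the models for being unable to show whether benefit builds up over sessions. The stated objectives do not ask that, and an effect averaged over cycles is a legitimate target.

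**Conclusion.** The point holds as a conditional, low-severity improvement to two secondary analyses. As specified, both models ignore which cycles a patient contributed. If outcomes trend over cycles and the arms differ in the number of periods observed, the group effect takes up part of the trend.

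Under the assumptions above, the rate ratio shifts by about 3% to 5% when stopping follows observed symptoms and by about 10% with strongly unequal stopping (13% in the most extreme case). The antiemetic odds ratio shifts by 12% to 17% under a strong trend. The direction follows the trend: with more stopping among controls, a falling trend flatters reflexology and a rising one works against it.

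A reader might infer that the planned models will report a time trend as a treatment effect. The documents do not support that, because they state neither condition and the distortion vanishes without both. Nor does the point touch the primary endpoint, a VAS change measured within the second cycle. The count of three periods is inferred from the diary window; the text on antiemetic use mentions cycles without a number.

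**What to change.** In Type of Statistical Analysis Used, add intercycle period as a categorical fixed effect to both the mixed Poisson and the mixed logistic model, beside group and the stratification criteria. Keep the days offset and the random intercept. Report, by arm, how many periods patients contributed, so that readers can see whether the imbalance arose.

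The cost is a change of wording and two degrees of freedom per model (three periods); no new data are needed. The term removes the artefact of the trend. It does not remove bias from stopping that depends on outcomes not observed, so the counts of periods per arm are still needed for interpretation. A group-by-period term may be added as a supporting analysis, but it is optional and not part of this correction.

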##### Quality of Life

The benefits of foot reflexology on quality of life will be assessed by the relative change in the overall European Organization for Research and Treatment of Cancer Quality of Life Questionnaire (EORTC QLQ-C30) score [31]. The patient is asked to complete EORTC QLQ-C30 at the baseline and end of the study (fourth cycle of chemotherapy).

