##### Anxiety

The benefits of foot reflexology on anxiety will be assessed by the relative change in the overall Hospital and Anxiety Depression Scale (HADS) score [32]. The patient is asked to complete HADS at the baseline and end of the study (fourth cycle of chemotherapy).

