The comparison of self-image between the two groups will be done using a linear model adjusted on the baseline self-esteem evaluated with the Rosenberg scale. A possible transformation of the BIQ score will performed to satisfy the assumptions of the linear model.

The analysis will be performed according to the intention-to-treat principle, considering all patients that completed the endpoint evaluation in the group that was allocated to them by the randomization. The time point for the primary endpoint has been defined to minimize the risk of missing data.

For the primary endpoint, a secondary analysis will be performed per protocol, including patients with the endpoint assessment, and for whom the strategy allocated during randomization was fully implemented (ie, patients allocated to the foot reflexology group that did not receive four sessions of foot reflexology will be excluded from the analysis).

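### Quality of life and anxiety are compared by an unstratified Wilcoxon test on relative change, which is valid but uses the baseline scores and the randomisation strata inefficiently

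*Protocol article*

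**What the plan says.** Under Secondary Outcomes, quality of life is "assessed by the relative change in the overall European Organization for Research and Treatment of Cancer Quality of Life Questionnaire (EORTC QLQ-C30) score", and anxiety is "assessed by the relative change in the overall Hospital and Anxiety Depression Scale (HADS) score". Each questionnaire is filled in twice. For quality of life, "The patient is asked to complete EORTC QLQ-C30 at the baseline and end of the study", the end of study being the fourth cycle; the Anxiety section gives the same two times for the HADS.

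The analysis is fixed in one sentence of Type of Statistical Analysis Used: "The comparison of quality of life and anxiety between the two groups will be done using a Wilcoxon test". It names no strata and no covariate.

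Under Trial Design, "Randomization is stratified on the type of cancer (digestive system or lung) and the presence or absence of metastases". The analysis section uses both factors in the linear model for the primary VAS endpoint, in the mixed Poisson model for episode frequency and in the mixed logistic model for antiemetic use. If the primary model's assumptions fail, the fallback is the van Elteren test, which is a stratified Wilcoxon test. Body image is analysed "using a linear model adjusted on the baseline self-esteem evaluated with the Rosenberg scale", with no mention of the strata.

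**The concern.** Three features of the planned comparison work against it.

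- **Baseline.** A pre-treatment score on the same instrument is available for every patient who completes it. Dividing by that score is usually a less precise way to use it than regressing on it.
- **Scale.** Relative change does not exist for a patient whose baseline score is 0, and a small baseline turns a small shift into a very large ratio. The article states no rule for such patients.
- **Strata.** The two randomisation factors are used in three other models of the same section, but not for these two outcomes or for body image. No reason is given.

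Quality of life and anxiety are named secondary objectives, and the Discussion expects a benefit on both. What is at stake is precision: with 80 patients, a real effect may be missed that the same data could have shown.

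**Working it through.** **The plan's own figure.** The only sample-size figure concerns the VAS endpoint: difference 73.5 − 49.5 = 24 points, SD 32.2, two-sided 5%, power 90%.

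n per group = 2 × (1.960 + 1.282)² × 32.2² / 24² = 37.8, so 38. The t-test version gives 38.8, so 39. At 40 per group, power is 91.5% (normal) or 90.9% (t). The stated 40 is reproduced, but it says nothing about power for quality of life or anxiety.

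**Simulation of the planned test.** The documents give no effect size, SD, correlation or score distribution for these outcomes, so all of the following are assumptions:

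- 40 per group, true effect 0.5 SD, 2,000 runs per setting;
- baseline to follow-up correlation rho of 0.3, 0.5 or 0.7;
- scale A, a quality-of-life type score: 0–100, mean 60, SD 22, in steps of 100/12;
- scale B, an anxiety type score: 0–21, mean 7, SD 4, in steps of 1;
- each stratification factor has an effect of 0 or 0.4 SD on the follow-up score.

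Power (%) when the effect raises the score:

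| Scale | rho | Strata effect (SD) | Wilcoxon, relative change | Linear, baseline | Linear, baseline + strata | Last minus Wilcoxon |
|---|---|---|---|---|---|---|
| A | 0.3 | 0 | 38.8 | 61.4 | 61.4 | 22.6 |
| A | 0.3 | 0.4 | 36.0 | 58.4 | 61.8 | 25.8 |
| A | 0.5 | 0 | 49.4 | 68.8 | 69.0 | 19.6 |
| A | 0.5 | 0.4 | 46.4 | 66.4 | 70.1 | 23.7 |
| A | 0.7 | 0 | 68.3 | 84.2 | 84.3 | 16.0 |
| A | 0.7 | 0.4 | 63.4 | 80.0 | 83.4 | 20.0 |
| B | 0.3 | 0 | 40.5 | 65.2 | 65.1 | 24.6 |
| B | 0.3 | 0.4 | 35.5 | 59.4 | 62.4 | 26.9 |
| B | 0.5 | 0 | 47.4 | 70.8 | 71.0 | 23.6 |
| B | 0.5 | 0.4 | 46.9 | 68.8 | 72.2 | 25.3 |
| B | 0.7 | 0 | 71.2 | 86.0 | 86.0 | 14.8 |
| B | 0.7 | 0.4 | 64.2 | 81.0 | 84.7 | 20.5 |

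The loss runs from 14.8 to 26.9 points.

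**Share due to the strata.** Compare the two linear models. With no strata effect the gain is −0.1 to 0.2 points, that is, nothing. With 0.4 SD effects it is 3.0 to 3.7 points. The remainder comes from replacing a rank test on relative change by a model with baseline as covariate.

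**Direction of effect.** On an anxiety scale a benefit would normally be a fall. Repeating the scale B settings with the effect reversed (−0.5 SD, all else unchanged) gives, for Wilcoxon against the linear model with baseline and strata, without and then with strata effects:

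- rho 0.3: 45.5 v 60.9 and 44.1 v 62.1 (losses 15.4 and 18.0);
- rho 0.5: 56.5 v 68.9 and 54.8 v 69.3 (losses 12.4 and 14.5);
- rho 0.7: 78.8 v 84.6 and 72.7 v 85.4 (losses 5.8 and 12.7).

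The loss is smaller, but it is present in every setting.

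**Validity.** With no true effect, the Wilcoxon test on relative change rejected in 3.7% to 5.6% of runs, and all methods together in 3.4% to 5.6%. Simulation error at 5% is √(0.05 × 0.95 / 2000) = 0.5 points. There is no sign of an inflated error rate.

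**Undefined outcomes.** The chance of a baseline recorded as 0 is Φ((0.5 − 7)/4) = Φ(−1.625) = 5.2% on scale B, about 0.052 × 80 = 4 patients. On scale A it is Φ((4.17 − 60)/22) = 0.6%, less than one patient. These rates depend wholly on the assumed distributions; the article refers to an overall HADS score and gives no range.

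**The case against.** The best defence is that a Wilcoxon test is a sound, robust choice for bounded and skewed questionnaire scores. Ranks limit the leverage of extreme ratios. The outcomes are secondary, and no power is claimed for them. All of that stands: replacing the test improves the plan and does not repair an invalid one. The power figures also rest on inputs that the documents do not supply.

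Four stronger readings are tempting and are not supported.

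- **That the baseline scores are ignored.** They are the reference and the denominator of the relative change. They are only not adjusted for.
- **That readers will get a p-value and no effect estimate.** The article names a test and is silent on the accompanying estimate, which may well stand in the full protocol or the analysis plan. The silence is not a finding.
- **That omitting the strata makes the inference invalid.** The simulated error rates show otherwise, and the gain from adding the strata is small.
- **That 80 patients could be made to act like about 107.** This comes from the variance ratio (1 + rho)/2 of a baseline-adjusted model to a change score: 0.75 at rho = 0.5, and 80/0.75 = 107. The ratio applies to a comparison of mean absolute change with equal variances at both times. The plan has a rank test on relative change, so the figure does not describe it.

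It is likewise not stated that patients with a baseline of 0 will be dropped. The article only leaves their outcome undefined.

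**Conclusion.** The concern holds as one of efficiency and of outcome definition. The article fixes both the relative-change outcome and the unstratified test, so the choice is open to review without sight of the analysis plan. It is also out of line with the rest of the section, which adjusts for the strata in three models and already names a stratified rank test.

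Under the assumed inputs, the cost against a linear model with baseline and strata is about 15 to 27 power points for an effect that raises the score. It is about 6 to 18 points for one that lowers the assumed anxiety score. The baseline covariate accounts for most of it and the strata for about 0 to 4 points. In addition, the outcome is undefined at a baseline of 0. Neither bias nor an inflated type I error is shown. Because the endpoints are secondary, the priority is moderate to minor.

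**What to change.** Analyse the fourth-cycle QLQ-C30 and HADS scores with a linear model on arm, baseline score of the same instrument, cancer type and metastatic status. Report the adjusted mean difference with its 95% confidence interval. This needs no ratio, so a patient with a baseline of 0 stays in the analysis.

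Keep van Elteren as the rank-based fallback or sensitivity analysis, as for the primary endpoint, preferably on absolute change so that the same patients contribute. Change the outcome definitions under Quality of Life and Anxiety to match. For consistency, add cancer type and metastatic status to the body-image model.

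The cost is a few sentences and minor programming. No new data are needed, since the baseline scores and strata are already collected. The change should be dated before the outcome data are analysed.
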